### Study design

The study design is an unblinded randomised control study with parallel arms where participants will be randomly allocated (1:1) to either the remote monitoring arm or usual care arm.

Following informed consent, baseline clinical data collected as part of usual clinical National Health Service (NHS) care will be used for the purpose of the study including previous medical history, all medication usage, previous lung function tests and radiology results. All participants will be asked to complete HRQoL questionnaires (modified Medical Research Council (mMRC) dyspnoea scale, K-BILD Questionnaire, EuroQol 5-Dimension 5-Level (EQ-5D-5L) questionnaire, Generalised Anxiety Disorder-7 (GAD-7) questionnaire) and Patient Activation Measure (PAM) at baseline.

Participants will then be randomly allocated to either the remote monitoring arm or usual care arms.

Remote monitoring arm:

Participants who are allocated to the active remote monitoring arm will be provided with a portable handheld spirometer (Spirobank Smart, MIR, www.spirometry.com) and pulse oximeter (model 3230, Nonin; www.nonin.com) linked to an electronic health application (patientMpower, www.patientMpower.com). Participants will be trained to undertake remote spirometry and pulse oximetry and they will be asked to perform measurements three times per week including two spirometry blows and one resting pulse oximetry reading on each occasion. All readings will automatically be captured via the patientMpower electronic health application and will be immediately visible to their clinical care team via a secure web-based portal. All spirometry attempts will be analysed in real time using artificial intelligence software (ArtiQ, www.artiq.eu)^29^ to assess the quality of the spirometry according to European Respiratory Society (ERS)/American Thoracic Society (ATS) criteria^20^ provided with real time feedback given to participants. Participants will be reminded to record their measurements once weekly.

Participating centres will be asked to monitor these remotely recorded measurements at least every 2 weeks and at, or before, planned clinical assessments. They will be advised that should there be a sustained decrease in either spirometry or pulse oximetry further clinical assessment is recommended.

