Participants should continue to have all clinical appointments and medications as per their treating clinician’s recommendations. If there is a clinical decision to discontinue remote monitoring—either for safety/clinical reasons or due to patient choice this should be recorded in the electronic case report form (eCRF).

Usual care arm: These participants will have all clinical appointments and medications as per their treating clinicians’ recommendations.

All participants will be asked to complete health-related QoL questionnaires at 3 months (K-BILD, GAD-7), 6 months (K-BILD, GAD-7, EQ-5D-5L, PAM, modified MRC dyspnoea scale) and at 12 months which is the conclusion of the study.

All clinical observations, appointments, investigations and conversations which occur over the course of the following year will be recorded in the eCRF and analysed.

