#### Data analysis plan

The objective of the primary analysis is to determine if the availability of spirometry within 2 weeks of the date of the first and last clinical review within the observation period is independent of the method by which it was obtained (ie, usual care with remote monitoring of spirometry or usual care alone). The primary endpoint variable is the number of outpatient clinical reviews for which spirometry data are available in the 2 weeks prior to the review. The primary endpoint will be assessed at the first and last outpatient clinical review in all patients who have ≥2 clinical reviews during the study observation period. The primary endpoint will be assessed by a χ^2^ test of independence.

All other endpoints will be summarised for descriptive statistical display.

The health economic analysis will be performed adopting the perspective of the NHS and Personal Social Services. NHS healthcare resource utilisation will be assessed using the data from the study and using standard unit cost data (Personal Social Services Research Unit), staff cost time and NHS tariffs. Effectiveness will be measured in terms of differences in quality-adjusted life-years in the two arms, using a linear approximation method, assuming the change in the utility over time is linear. Costs and effectiveness in both arms will be compared and the results presented in terms of incremental cost-effectiveness ratio.

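### The listed cost sources name nothing for the remote arm's devices, application and software, and no baseline adjustment of the QALY difference is stated

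*Protocol article*

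**What the plan says.** The economic method is set out in the last paragraph of the Data analysis plan section of the protocol article.

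- **Perspective:** "The health economic analysis will be performed adopting the perspective of the NHS and Personal Social Services".
- **Cost inputs:** NHS resource use recorded in the study, valued "using standard unit cost data (Personal Social Services Research Unit), staff cost time and NHS tariffs".
- **Effect:** "Effectiveness will be measured in terms of differences in quality-adjusted life-years in the two arms, using a linear approximation method".
- **Output:** "Costs and effectiveness in both arms will be compared and the results presented in terms of incremental cost-effectiveness ratio".

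The Outcomes section lists three health economic endpoints: staff time spent on the data portal, contacts with the monitoring team, and respiratory admissions.

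The Study design section describes what the remote arm receives. Its participants are "provided with a portable handheld spirometer (Spirobank Smart, MIR, www.spirometry.com) and pulse oximeter (model 3230, Nonin; www.nonin.com) linked to an electronic health application". AI software grades every blow, and participants are trained in the measurements.

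The same section has all participants complete a baseline set that includes the "EuroQol 5-Dimension 5-Level (EQ-5D-5L) questionnaire, Generalised Anxiety Disorder-7 (GAD-7) questionnaire) and Patient Activation Measure (PAM) at baseline". Follow-up questionnaires come at 3 months (without EQ-5D-5L) and then at "6 months (K-BILD, GAD-7, EQ-5D-5L, PAM, modified MRC dyspnoea scale) and at 12 months which is the conclusion of the study". The Assignment of arms section stratifies randomisation by ILD-GAP stage and by secondary or tertiary centre.

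**The concern.** Cost-effectiveness is half of the stated study objective, and this one paragraph is all that the article says about how it will be estimated.

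**Cost.** The paragraph does more than promise to measure costs: it lists the inputs. The items that distinguish the remote arm (two devices, an application and quality-control software) appear neither in that list nor among the economic endpoints. They are supplied for the trial and to one arm only, so they may not surface through routine capture of NHS resource use. If the list is followed literally, the error runs in one direction, and randomisation does nothing to correct it.

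**Effect.** Baseline EQ-5D-5L is part of the area under the utility curve and also predicts the later scores. It is not a stratification factor. An arm difference that ignores it keeps all the chance imbalance in baseline utility, and that noise can be as large as a small QALY effect. The trial was sized on spirometry availability, not on QALYs.

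**Working it through.** The article states no QALY, cost or ICER figure, so there is none to reproduce. The only document number needed is the sample size: 108 / 0.82 = 131.7, rounded up to the planned 132. The 108 expected completers give 108 / 2 = 54 per arm.

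**Cost: inputs set side by side**

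| Remote-arm input (Study design) | Source or endpoint named? |
|---|---|
| Staff review of the portal | Yes: endpoint, and staff time is costed |
| Contacts with the monitoring team | Yes: endpoint |
| Handheld spirometer, pulse oximeter | None named |
| Application licence | None named |
| AI spirometry quality software | None named |
| Set-up and participant training | Not itemised (staff time is costed in general) |

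If a cost D per remote-arm participant is left out, incremental cost is too low by D. For a positive QALY gain the ICER is then too low by D / ΔQALY. The article gives no prices, so both inputs below are assumptions, used only to show scale:

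- D = £200, ΔQALY = 0.04: 200 / 0.04 = £5,000 per QALY
- D = £500, ΔQALY = 0.02: 500 / 0.02 = £25,000 per QALY
- D = £1,000, ΔQALY = 0.01: 1,000 / 0.01 = £100,000 per QALY

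**Effect: chance baseline imbalance**

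Assumptions, none of them given in the article: EQ-5D-5L at 0, 6 and 12 months; utility SD 0.15 to 0.30, equal at each visit; correlation ρ of baseline with each later score 0.5 to 0.9.

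1. Linear interpolation over one year: QALY = 0.5 × (U0 + U6)/2 + 0.5 × (U6 + U12)/2 = 0.25·U0 + 0.50·U6 + 0.25·U12.
2. With equal SDs, a baseline difference d carries an expected ρd into each later score. The share of d that reaches the QALY difference is 0.25 + 0.75ρ: 0.625 at ρ = 0.5, 0.775 at 0.7 and 0.925 at 0.9.
3. The standard error of the baseline arm difference is SD × √(2/54): 0.0289 at SD 0.15 and 0.0577 at SD 0.30.
4. QALY difference created by one standard error of imbalance (step 2 × step 3):

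| SD | ρ = 0.5 | ρ = 0.7 | ρ = 0.9 |
|---|---|---|---|
| 0.15 | 0.018 | 0.022 | 0.027 |
| 0.20 | 0.024 | 0.030 | 0.036 |
| 0.25 | 0.030 | 0.037 | 0.045 |
| 0.30 | 0.036 | 0.045 | 0.053 |

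Multiplying by 1.96 gives a 95% range of about ±0.035 to ±0.105 QALY across the grid. With all 66 randomised per arm the middle case barely changes: at SD 0.20 and ρ = 0.7, 0.20 × √(2/66) × 0.775 = 0.027, against 0.030 with 54.

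**The case against.** The strongest reply is that a condensed article is being read as if silence were a decision. Much of that stands.

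- **Device cost.** A reader might infer that the ICER omits the cost of the intervention. The text does not say so. The listed sources are attached to NHS resource use, and a separate sentence compares costs in both arms without confining them to those sources. Staff review time and contacts are explicitly collected. What remains is narrower: the article enumerates its inputs, and no listed source covers the equipment and licences.
- **Adjustment.** A reader might infer that the trial has chosen a raw arm difference. The linear approximation describes how the QALY is built, not how the arms are compared, and a regression coefficient is also a difference between arms. Adjustment may be specified in an analysis plan that is not shown.
- **Bias.** Under 1:1 randomisation an unadjusted QALY difference is unbiased, and chance imbalance is sampling error already reflected in its standard error. The gain from adjustment is precision, not removal of a systematic error.
- **Reporting.** The article does not say that the ICER will be the only result presented. Intervals and acceptability curves are detail that an article normally leaves to the analysis plan, so their absence is no finding.
- **Schedule.** The instruments used at 12 months are not itemised in the text and the timeline figure is not shown, so EQ-5D-5L at 12 months is an inference.

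**Conclusion.** The point holds in a limited form, and the cost side is the firmer half. The listed cost sources and economic endpoints leave the remote arm's devices, application and software without a source. If costing follows that list, incremental cost and the ICER favour remote monitoring. The size cannot be fixed from the article because it gives no prices; the £5,000 to £100,000 per QALY range above rests wholly on assumed costs and gains.

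The QALY side is a matter of precision. No baseline adjustment is stated, although the covariate is collected from everyone. Under the stated assumptions an unadjusted difference carries about 0.018 to 0.053 QALY per standard error of chance imbalance.

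The documents do not support the claim that device costs are excluded or that adjustment has been ruled out. The primary endpoint is unaffected.

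**What to change.** Amend the economic paragraph of the Data analysis plan before any comparison of the arms is made:

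1. State that the acquisition or licence cost of the spirometer, oximeter, application and AI quality software, plus set-up and training time, is added to the cost of each remote-arm participant, and name the price source.
2. State that incremental QALYs are the arm coefficient from a regression of QALY on arm, baseline EQ-5D-5L, ILD-GAP stage and centre type (secondary or tertiary).

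No new participant questionnaire is needed for the adjustment, since baseline EQ-5D-5L is already collected; the prices would have to be obtained from the suppliers or purchase records. The cost is a higher, less favourable figure for the remote arm and slightly more analysis work.

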Informed consent will be obtained by the principal investigator and/or a nominated deputy as recorded on the sponsor’s delegation of responsibilities log. All participants will confirm their informed consent either in writing or electronically through the REDCap electronic consent form (online supplemental document 1).^38^

10.1136/bmjresp-2023-002067.supp1Supplementary data

#### Safety reporting

No significant safety concerns are anticipated in relation to any measurements carried out as part of this study. All adverse events will be recorded and closely monitored until resolution, stabilisation or until it has been determined that the study intervention is not the cause. The chief investigator shall be informed immediately of any serious adverse events and shall determine seriousness and causality in conjunction with any treating medical practitioners.

### Patient and public involvement

Representatives of the APF charity are active members of the study group and have contributed to the design of the study and attend the fortnightly meetings to monitor the study’s progress. All patient-facing documentation has been reviewed together with patient representatives and user experience evaluation has been developed alongside patients both with and without prior experience of remote monitoring. APF will also support recruitment and dissemination of study findings to participants and the wider ILD community.

#### Confidentiality

All data will be handled in accordance with the Data Protection Act 2018.

Personally identifiable data (PID) is marked on the eCRF so that it can be excluded on data download for analysis. Subject initial and trial identification number (ID) will be used for identification. Further PID is only included for the use of the electronic consent form.

PID is required for the conduct of the remote monitoring arm in order to set up the remote monitoring and also in order to provide equipment to participants. A data processing agreement is in place to support this data sharing under the Data Protection Act.

CRFs have been designed by the CI and the final version approved by the sponsor and ethics committee. All documents will be stored safely in confidential conditions. On all study-specific documents, other than the signed consent form, the participant will be referred to by the study participant number, not by name.

All investigators will have access to the anonymised data set for the purpose of analysis only and it will be stored by the sponsor.

#### Dissemination

All data will be anonymised and grouped for presentation and publication. The results from this study will be publicised at regional and national conferences as well as being submitted for publication in open access peer-reviewed journals in accordance with UK Research Council policies. No participants will be identified in any publications that arise from this research.

## Conclusion

REMOTE-ILD is a randomised controlled trial of remote monitoring of home spirometry and pulse oximetry in patients with ILD which will compare clinical and health economic outcomes to that of usual clinical care over 12 months.

## Data Availability

Data sharing not applicable as no datasets generated and/or analysed for this study. Anonymised aggregate data will be shared on reasonable request as detailed in the ethics approval.
